### Adverse events

Botulinum toxin has favorable safety and tolerability profile [26]. The list of adverse events will be looked for are i) injection site pain [27] ii) skin rash [28], and iii) transient muscle weakness or weakness observed beyond the site of local injection [29]. Potential for antibody formation can be minimized by using minimum effective dose and spacing the injection schedule [30]. In the event of any adverse events, the participant will be encouraged to contact the study physician. If noted, data will be collected regarding adverse effects. Rights of withdrawal without prejudice to future treatment at any time in the study will be emphasized.

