### Procedures

Participants will undergo assessments at base line, 3 weeks, 3 months and 5 months following the injection (Fig. 1). All primary and secondary outcomes will be measured at all 4 time points. Additionally, the demographic and health characteristics such as age, gender, weight, type of stroke, affected side and mean time since stroke will he determined. A sensory evaluation will also be carried out in all the participants in the RCT.

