### Routine physiotherapy and standard care

All participants in the study will receive physiotherapy and standard care such as orthotics (both in the intervention and the control group). This will include stretching, balancing, strengthening exercises and gait retraining. Gait retraining (task specific) will include walking on the level ground and then progressing to walking on inclines and different surfaces. Therapy will be standardized in terms of frequency (two sessions/week in the Physiotherapy department at the Queen Elizabeth Hospital, duration (45 min each session) and intensity (4–6 in Borg’s Scale of Perceived Exertion i.e. somewhat hard and hard). Patients will also be given a home exercise program. Compliance will be recorded monthly where participant activity will be recorded through phone calls. Additionally, phone calls will be made to encourage and motivate participants whereby they will be given advice about diet, weight and activity management. Activity at home will be monitored by ActivPal in sample subjects.

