## Discussion

This RCT protocol is carefully designed for evaluating the effectiveness of BT in improving the exercise program outcomes in the intervention group compared to the control group with increased effects on walking and other lower limb functioning and improved QOL and ADLs.

Improved walking is one of the highest priorities for people living with stroke [34]. Walking is a mode of bipedal locomotion in which both feet remain in contact with the ground, followed by a period of single stance on one limb while the other limb is swung forward. Post stroke patients with equinovarus deformity are unable to achieve proper contact with the ground resulting in poor stance on the affected leg and lose the heel toe rhythm of walking due to plantarflexion/inversion of the foot. Most of the phases of gait such as initial contact, loading response, mid stance, push off (stance phase), initial swing, and mid swing (swing phase) are affected. The awkward positioning of the foot and spasticity impairs balance, transfer, stride, gait and mobility besides causing spasm and pain. The awkward positioning can also lead to fall and fractures [35]. There is significant human and economic cost of spasticity [36]. Inability to walk is a predictor of losing independence and/or discharge to a nursing home [37]. Above all spasticity contributes to a range of adverse health outcomes including mortality [38]. In the upper limbs, there is no related dependence of operation. If one side of the body is affected, following stroke, the other side can be trained to compensate. In the lower limb, the dependence of both legs is essential for standing, maintaining balance, transferring from sitting to standing position and walking ability. This emphasizes the fact that rehabilitation of the lower extremities is very important. This study will achieve measurable important methodological and statistical outcomes, which can be replicated by other studies. The study has the methodological rigor of a placebo control trial. All participants will be provided with the standard care. At the end of the study the BT and placebo treated participants will be offered BT injection.

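### The adverse events section describes only participant-initiated reporting, gives no method or timing for the events it says are sought, and does not list falls, although visits and monthly calls to both arms already exist

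*Protocol article*

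**What the plan says.** The Adverse events section of the protocol article opens with a list: "The list of adverse events will be looked for are i) injection site pain [27] ii) skin rash [28], and iii) transient muscle weakness", the last item extending to weakness away from the injection site. It attaches no person, time point or question to that search. Two sentences then describe how an event comes to be recorded: "In the event of any adverse events, the participant will be encouraged to contact the study physician" and "If noted, data will be collected regarding adverse effects".

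Other sections describe regular contact with participants in both arms:

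- Procedures: "Participants will undergo assessments at base line, 3 weeks, 3 months and 5 months following the injection (Fig. 1"). The primary and secondary outcomes are measured at all four time points. Adverse events are not named among them.
- Routine physiotherapy and standard care: "two sessions/week in the Physiotherapy department at the Queen Elizabeth Hospital", and "Compliance will be recorded monthly where participant activity will be recorded through phone calls". The other stated uses of the calls are encouragement and advice on diet, weight and activity.

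On falls, the Discussion says of the foot position in these patients: "The awkward positioning can also lead to fall and fractures". Falls do not appear in the Adverse events section or among the outcomes.

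**The concern.** How events are sought determines how many are found. If recording starts with the participant deciding to call, events that are mild, short-lived or not attributed to the injection tend to go unrecorded. Transient weakness and a fall at home without serious injury are of that kind.

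Falls matter in this trial for reasons its own text supplies. The injected muscles are in the leg, weakness is a listed event, gait training progresses to inclines and varied surfaces, and the primary outcome is walking. More falls through weakness would be a plausible harm, and fewer falls through better foot position a plausible benefit. The three-item list is set up to show neither.

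The authors want the result to support a change in funding policy. Event rates by arm are a natural part of that evidence, and events not asked about during follow-up cannot be fully recovered later.

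**Working it through.** **1. The stated method beside the stated contacts.**

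| Contact | Where described | Stated purpose | Tied to adverse events? |
|---|---|---|---|
| Participant contacts the physician | Adverse events | Report an event | Yes |
| Visits at 3 weeks, 3 months, 5 months | Procedures | Primary and secondary outcomes | Not stated |
| Monthly phone calls | Routine physiotherapy and standard care | Compliance, activity, motivation, advice | Not stated |
| Physiotherapy twice a week | Routine physiotherapy and standard care | Therapy | Not stated |

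The list implies some search for three events, without method or timing. For any other event, falls included, the first row is the only route described. The visits alone leave long gaps for a transient event: taking 3 months as about 13 weeks, 13 − 3 = 10 weeks pass between the first two post-injection visits. The monthly calls would shorten that gap.

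**2. The plan's own figure.** The Adverse events section contains no number. The one input the document supplies is the group size, which reproduces. A difference of 0.13 with SD 0.13 (standardised difference 1.0), two-sided 5% and 90% power, needs 22.02 per group by the t-test, rounded up to 23. Then 23 × 1.5 = 34.5, rounded to 35, and 35 / 0.75 = 46.7, rounded to 47.

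**3. What incomplete capture does.** Let p₁ and p₀ be the true proportions affected on BT and placebo, and c the fraction captured, equal in both arms.

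- Expected recorded count per arm = 47 × c × p
- Recorded risk difference = c × (p₁ − p₀), which shrinks in proportion to c
- Recorded risk ratio = (c × p₁) / (c × p₀) = p₁ / p₀, unchanged

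**4. Illustration.** The document gives neither event rates nor a capture fraction, so p₁ = 20%, p₀ = 5% and every value of c are assumptions. Power is for a two-sided Fisher test at 5%, by exact enumeration.

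| c | Expected affected, BT vs placebo | Risk difference | Risk ratio | Power |
|---|---|---|---|---|
| 100% | 9.4 vs 2.4 | 15 points | 4 | 47% |
| 75% | 7.1 vs 1.8 | 11.25 points | 4 | 30% |
| 50% | 4.7 vs 1.2 | 7.5 points | 4 | 14% |
| 30% | 2.8 vs 0.7 | 4.5 points | 4 | 3% |

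With a smaller assumed contrast, 10% vs 5%, power is 5.6% at full capture and 1.0% at half.

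For an event with true incidence 5% in one arm, the chance of recording none is (1 − 0.05c)⁴⁷: 9% at c = 100%, 30% at 50% and 49% at 30%.

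The Statistical methods section describes no between-arm test of adverse events, so the power column only shows how information is lost. The counts and the chance of recording no event are the more relevant columns.

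**The case against.** **Capture is not stated to be passive only.** A reader might infer that an event is recorded only if the participant contacts the physician. The text does not say so. The three events are to be looked for, which is investigator-side wording, and the sentence on collecting data does not say who notes the event. Staff also see participants at physiotherapy twice a week and could notice weakness or a rash, or be told of a fall. This stands. The defect is an unspecified search beside a participant-initiated route, not a proven absence of any other route.

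**An article condenses.** Forms, visit checklists and reporting windows commonly sit in a full protocol that is not shown, and the stated purposes of the calls do not exclude others. This stands for forms and windows, whose absence is no fault. It does not dispose of the point, because the article does describe a reporting route, and that route is a weak one.

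**Falls may already be covered.** The instruction refers to any adverse event, which can include a fall, and the Discussion attributes falls to the condition and not to the drug. Both are correct. A fall is reportable, but nothing prompts the participant or staff to report it.

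**Under-counting and a damaged safety comparison are not documented facts.** A reader might infer that events will be under-counted and that a planned comparison between arms will be spoiled. The document gives no rates or capture fraction and plans no such comparison. Blinding makes unequal reporting less likely, though it does not exclude it. Low power for harms also comes largely from 47 per arm, which better questioning does not change.

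**Conclusion.** The point holds as a low-cost improvement to a stated method. The article describes participant-initiated reporting, leaves the search for its three listed events without method or timing, and does not prompt for falls, although its own text makes falls relevant. Followed as written, mild or transient events and falls are likely to be incompletely recorded in both arms.

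The consequence is lower absolute rates and a smaller risk difference. If capture is equal in the two arms, the risk ratio is not biased. The treatment could therefore look safer on the absolute scale, but the document gives no ground for claiming a bias in relative risk.

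The size of the effect is unknown. Every figure for incomplete capture rests on assumed incidence, assumed capture and equal capture in both arms. Neither the sample size nor the primary analysis is affected.

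**What to change.** In the Adverse events section, replace the present reporting sentences with a fixed schedule of enquiry:

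- At the 3-week, 3-month and 5-month visits and at each existing monthly call, blinded study staff ask every participant in both arms the same questions.
- The questions cover injection-site pain, rash, local or distant weakness, falls (number, and whether with injury or fracture), and one open question about anything else.
- Participant-initiated contact with the study physician is kept as an addition.
- Adverse events and falls are reported by arm.

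If the full protocol already contains such questions, a sentence in the article saying so is enough, provided falls are among them.

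The cost is a few minutes per contact, one form, and more minor events recorded in both arms. Sample size, visit schedule and treatment stay as they are.

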### Qualitative evaluation

A qualitative study will be undertaken to understand the phenomena of participants experience of their condition/s and the impact of the intervention and how this differs between the participants in the control and intervention group. The qualitative study has an important function in understanding the participants established and changing experiences and outcomes. The findings from the qualitative data will enhance the findings from the quantitative data and may lead to new study questions [31, 32].

We plan to interview approximately 10 participants in each arm before intervention and follow up at 3 weeks and 5 months (*N* = 20) (or until data saturation is achieved) [33]. Every 4th participant will be invited in this semi structured interview. The first interview will start with broad questions about their condition/s and their effect; e.g. how they currently understand/perceive their condition, what limitations these impose on their lives and their expectation of the impact of the intervention. The second interview will focus on the immediate impact of the intervention. The third interview will focus on longer term impact. The person collecting and analyzing the data will be blinded to the study group.

### Sample size calculation

In most of the RCT’s included in our systematic review sample inadequacies were identified. Chief among these was the problem of inadequate sample calculations for repeated measures design. In repeated measures studies, within patient observations are correlated which often results in an estimate of the standard deviation that is an underestimate of the true standard deviation. Failure to account for this leads to an increased in the risk of a Type 1 error. In this study, we inflated our sample size by applying a design effect (DEFF) of 1.5 to account for the repeated measure design. Calculations were based on the requirement that effects be detected at the 5% alpha level with 90% statistical power. Based on available evidence, it was assumed that the clinically meaningful difference between the two treatment groups would be 0.13 points in gait speed with a standard deviation of 0.13. Based on these assumptions, a sample of 35 patients per group is required following the application of the design effect (*n* = 23 * DEFF). We have further inflated the sample size to *n* = 47 per group to account for an expected attrition rate of 25%.

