### Statistical methods

An intention-to-treat (ITT) and per-protocol analysis is planned. The data will be summarized using means with standard deviations and medians with inter-quartile range. Counts and percentages will be used to describe categorical measures. Baseline characteristics will be assessed to identify any differences between treatment groups that would require adjustment in subsequent analyses. A linear mixed effects model will be applied to assess treatment effects over time. Pairwise, post hoc comparisons will be made using the Student t-test. All tests will be two-tailed and assessed at the 5% alpha level.

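### The design effect of 1.5 for repeated measures does not justify raising the patients needed from 23 to 35 per group; the surplus is a margin and should be stated as one

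*Protocol article*

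**What the plan says.** The section on sample size calculation (protocol article) asks that "effects be detected at the 5% alpha level with 90% statistical power". The effect assumption is "0.13 points in gait speed with a standard deviation of 0.13", a standardised difference of 1. The section argues that observations within a patient are correlated, that the SD is therefore often estimated too low, and that "Failure to account for this leads to an increased in the risk of a Type 1 error". As the remedy, "we inflated our sample size by applying a design effect (DEFF) of 1.5 to account for the repeated measure design". The result is that "a sample of 35 patients per group is required following the application of the design effect", with the pre-inflation figure of 23 shown, and 47 per group after allowing for 25% attrition (94 in total).

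Elsewhere, the consent and randomization section has patients randomised individually. The procedures section measures every outcome at baseline, 3 weeks, 3 months and 5 months. The statistical methods section plans a linear mixed effects model and adds: "All tests will be two-tailed and assessed at the 5% alpha level". The article gives no within-patient correlation and no derivation for the 1.5. It does not say whether 0.13 is the SD of a single visit, of change from baseline, or of a baseline-adjusted outcome.

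**The concern.** A design effect of the form 1 + (m − 1)ρ, with m measurements per patient and within-patient correlation ρ, tells how many correlated observations are worth a given number of independent ones. The figure of 23 is already a count of independent patients with one measurement each. Multiplying it by a repeated-measures design effect treats further visits by the same patient as if they removed information.

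The Type 1 error argument does not lead to a larger sample either. If m·n correlated observations are analysed as independent, the variance of a group mean is taken as σ²/(mn) when it is σ²[1 + (m − 1)ρ]/(mn). The ratio of the two, 1 + (m − 1)ρ, does not depend on n, so more patients leave the problem as it was. Modelling the correlation solves it, and the planned mixed model does that.

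At stake is whether the required size and the 90% power describe this design. The real tolerance for a wrong SD or a smaller effect is also hidden behind a reason unrelated to it. The section offers the step as its answer to inadequate calculations in earlier trials, so others may copy it.

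**Working it through.** **Inputs.** From the sample size section: difference 0.13, SD 0.13, alpha 5%, power 90%, design effect 1.5, attrition 25%. Two-sided testing is from the statistical methods section. Equal allocation is inferred from the equal group sizes (47 + 47 = 94).

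**Reproducing the plan's figures.**
- Normal approximation: n = 2(z₀.₉₇₅ + z₀.₉₀)²(SD/difference)² = 2(1.960 + 1.282)² × 1 = 21.01, so 22 per group.
- Exact two-sample t-test (noncentral t): power 0.8997 at 22 and 0.9125 at 23, so 23 per group. This matches the plan. A one-sided test would give 18 by the normal formula and does not match.
- 23 × 1.5 = 34.5, rounded up to 35.
- 35/0.75 = 46.7, rounded up to 47.

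Every step reproduces once the 1.5 is accepted.

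**Power at the stated difference and SD** (t-test, two-sided 5%, 0.13 taken as the SD of the analysed contrast):

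| Evaluable per group | Power |
|---|---|
| 23 | 91.3% |
| 35 | 98.5% |
| 47 | 99.8% |

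Without the design effect, 23/0.75 = 30.7, so 31 per group or 62 in total, against 94 planned: a surplus of 32.

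**What repeat visits do to the number of patients.** For the mean of m visits the patient count is multiplied by [1 + (m − 1)ρ]/m, which is never above 1. The article gives no ρ, so a range is assumed. With m = 3 post-injection visits:
- ρ = 0.3: (1 + 0.6)/3 = 0.53, and 23 becomes 13.
- ρ = 0.9: (1 + 1.8)/3 = 0.93, and 23 becomes 22.

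For one visit adjusted for baseline the multiplier is 1 − ρ²:
- ρ = 0.3: 0.91, and 23 becomes 21.
- ρ = 0.9: 0.19, and 23 becomes 5.

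None of these exceeds 23.

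**What 35 evaluable per group really buys.** 90% power needs a standardised difference of 0.786.
- At SD 0.13, the difference is 0.786 × 0.13 = 0.102.
- At a difference of 0.13, the largest SD is 0.13/0.786 = 0.165.
- For a difference of 0.13 at other assumed SDs, power is 92% at 0.16, 76% at 0.20 and 57% at 0.25.

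**Premises under which a factor of 1.5 would be right.**
- The true variance is 1.5 times the assumed one: SD = 0.13 × √1.5 = 0.159. Then 35 per group give 92.0% power and 23 give 77.3%.
- 0.13 is a single-visit SD and the analysis is an unadjusted change score. The variance factor is 2(1 − ρ), which equals 1.5 at ρ = 0.25 and exceeds 1 for any ρ below 0.5.

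**The case against.** The best defence is that the 1.5 may have been intended as a variance inflation. The section does say that an SD from repeated measurements can be too low, and its own SD is taken from available evidence. Read that way, an SD of about 0.159 makes 35 per group a reasonable answer to a 90% target. Similarly, the outcomes section names change in gait velocity as primary, and an unadjusted change score with baseline correlation 0.25 would also need a factor of 1.5. The plan also does not rely on sample size alone, because the mixed model already handles the correlation.

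Part of this stands. The statement that 35 exceeds what 90% power needs depends on 0.13 being the SD of the analysed contrast, and the article does not settle that. But the article states neither an inflated SD nor a correlation. It labels the 1.5 as a design effect for repeated measures, and that reason fails for individually randomised patients under a mixed model. That the model already deals with the correlation is a further reason not to deal with it again in the sample size.

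A reader might infer an arithmetic slip; there is none, since 23, 35 and 47 follow from one another. A reader might also infer that the trial is underpowered or its analysis invalid. The documents do not support that: at the stated inputs the step adds patients, and it changes neither the test nor its level.

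**Conclusion.** The point holds as a fault in the justification and in the stated requirement. Conditional on 0.13 being the SD of the analysed contrast, 23 evaluable patients per group give about 91% power, 35 about 98.5% and 47 about 99.8%; 35 is therefore not the number needed for 90%. The Type 1 error rationale is wrong whatever the SD means. The error is conservative, so this is a should-fix. It would be too strong to say that the 35 is wrong under every reading, because a variance 1.5 times the assumed one, or a change score with correlation 0.25, would produce the same factor. It would also be too strong to say that enrolment must fall to 62: the surplus can serve as a margin, provided it is described as one. The figures rest on a two-sample t-test with equal groups, and the range of ρ is an assumption.

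**What to change.** Keep 47 per group and rewrite one paragraph:

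1. Delete the design effect and its Type 1 error rationale. Say that within-patient correlation is handled by the covariance structure of the mixed model.
2. State whether 0.13 is the SD of a single visit, of change, or of the baseline-adjusted outcome.
3. Present the extra patients as a margin, conditional on item 2. For example: *With 23 evaluable patients per group, power is at least 90% (about 91%) for a difference of 0.13 with SD 0.13. With 35 evaluable per group (47 randomised, 25% attrition), power is about 98% at these inputs, and 90% is kept for a difference of about 0.10 (0.102), or for 0.13 with an SD up to about 0.165.*
4. If the 1.5 was meant to allow for an SD estimated too low, say so and give the inflated SD (about 0.16, about 92% power at 35 per group) in place of a repeated-measures design effect.

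The cost is the rewording, with no change to enrolment or analysis.
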